## Abstract

**Background:**

The use of data in decision making and planning in primary health care settings is critical for improving efficiency and health outcomes for patients and communities. Implementation research can be used to fully understand the effects, context, challenges, and facilitators of data use, as well as how to scale up data use interventions. However, in the context of low resource settings, little is known about how implementation research can be employed to assess the implementation and impact of data use interventions.

**Methods:**

We will conduct a hybrid type 2 effectiveness-implementation study employing a mixed method controlled before and after design to measure the effects of data use interventions while simultaneously understanding the implementation of those initiatives. The controlled before and after entails measurement of the effects of the interventions at baseline and end line in a matched intervention and control health facilities using structured questionnaire to health workers (n = 440) and existing patients (n = 422) while also extracting selected health outcome variable from routine data in all participating health facilities (n = 80). The mixed methods component entails measuring the implementation outcomes (adoption, acceptability, fidelity and maintenance) and their moderators entails the integration of both quantitative and qualitative data collection, analysis, and interpretation (i.e. mixed methods) approach by using a structured questionnaire to implementers (health workers and managers) (n = 400). Experiential dimensions of implementation processes and moderators will be explored using qualitative interviews. Guided by implementation research theories and frameworks, a theory of change (TOC) is developed first to guide the evaluation of implementation processes and effects of the interventions. Descriptive and inferential statistics will be employed to analyze quantitative data whereas thematic analysis approach will be employed for qualitative data.

**Discussion:**

This study is one of the first to test the simultaneous measurement of effects and implementation processes of data use interventions in the primary health care settings. Findings will support efforts to improve quality of services by optimizing scale up and sustainability of the data use initiatives in primary health care settings.

## Introduction

In an effort to achieve the sustainable development goals (SDGs), specifically so goal number 3: good health and wellbeing, low and middle income countries (LMICs) are striving to hasten the pace under which health system strengthening initiatives are implemented [1, 2]. There is growing evidence on the importance of using quality and timely data from the health management information systems (HIMS) to inform the progress of health system strengthening initiates across all the WHO health system building blocks [3–5]. To achieve the targeted health system strengthening goals, quality data is required for the planning and implementation of each of the health system building blocks [6].Existing evidence indicates that positive data experiences lead to a need for more data and a sustained commitment to improving data quality and data use [5, 7]. In addition, there is a relationship of improved information, demand for data, and continued data use and this contributes to improved performance and unexpandable benefits of health programs and policies [4, 5].

Existing evidence also attests to the fact that few health facilities use data collected through the routine HIMS for decision making and planning [8–10]. While the use of data at health facility level has benefits in data driven decision making such as in budget preparations, staffing decisions, medical supply and planning clinical services, several factors have been implicated to influence it. The factors reported in literature include: governance (leadership, participatory monitoring, regular review of data and supervision) [9, 11, 12], type (level) of a health facility [13]; production of information (data analysis ,presentation of results, and data quality); health systems inputs (human workforce, financial resources) [9, 13] and health information system resources (electronic health management information systems, organizational structure, training) [11]. Proactive interventions that promote use of data in primary health care settings may hasten use of data for decision making and planning and therefore help to strengthen health systems. As such, data use initiatives that breakdown barriers to data use, improve availability of ready to use data and build capacity of health workforce to effectively use data may help to improve quality of care, strengthen health systems and hasten achievement of universal health coverage (UHC).

Based on the PRISM (*Performance of Routine Information Systems Management*) framework, for data use intervention to be effective, they should address inputs, processes and outputs or performance of routine health information systems (RHIS) [14]. The PRISM framework defined RHIS performance as better quality data and continuous use of information. RHIS performance is a function of RHIS processes and their technical, behavioral and organizational determinants. Addressing these determinants may lead to improved quality of care, better health outcomes and system performance.

In Tanzania, UNICEF and the Data For Implementation (Data.FI) project, funded by the United States Agency for International Development (USAID), are implementing a data use initiative in the primary health care settings with a goal of improving data use in decision making and planning at different levels, Data.FI providing support at the council level while UNICEF in collaboration with PORALG providing support at the facility level. The interventions are implemented in the two regions of Tanzania namely Dar es Salaam and Dodoma, in which two local government authorities (councils) in each of the region have been recruited in the intervention.

Interventions to address data use in primary health care settings are often complex with multiple components. Complex interventions require extensive stakeholder involvement, longer time frames, and are subject to strong contextual influences [15, 16]. As a result, they pose evaluation design and implementation challenges, necessitating a comprehensive approach to program evaluation and monitoring. Desirable evaluation designs are those that aim at: 1) understanding the implementation processes of the intervention and the moderating factors, specifically describing in detail the adoption, fidelity program reach, beneficiaries/client responsiveness and quality of implementation of key process indicators as well as sustainability indictors 2) Using the implementation outcomes to explain the probable variations of effects observed when measuring the impact of the program.

Intervention implementation strategies targeting data use determinants can improve implementation outcomes, such as adoption, acceptability, fidelity and sustainability. Supportive supervision and technical backstopping designed to overcome implementation barriers and leverage innovations to foster data use initiative implementation represent promising approaches to facilitate implementation [11, 17, 18].

Documenting and assessing program implementation processes, program effects, and understanding contextual factors that may affect both the implementation process and program effects in the context of health system strengthening is a critical component of any robust and comprehensive evaluation effort of complex health system interventions implemented in real-world settings. Studies that explicitly link implementation processes to program outcomes have been found to be informative when taking interventions into scale or implementing in other settings as it is easier to draw lessons [10, 11].There is a litany of evidence that the level and process of implementation affect the outcomes of a program [18–21]. It follows that assessing the implementation process of interventions offers potentials to describe the mechanisms through which a given intervention produces outcomes, thus documenting both expected and unexpected effects.

Finding from such evaluations contribute to continuous learning and lesson drawing across settings in the stride forwards to strengthen health systems as countries strive to move towards universal health coverage (UHC). In the data use domain, little is known on how the interventions are implemented, the effectiveness of the intervention and the influence of contextual factors in relation both to implementation and outcomes of the interventions.

The objective of this study is to disentangle the implementation processes of data use initiatives (adoption, acceptability, fidelity, maintenance, and cost), understand the determinants of implementation outcomes, and determine the effects of data use initiatives on quality of care and selected health outcomes.

In this protocol, we aim to unravel the implementation processes (adoption, acceptability, fidelity, maintenance and cost) of the data use initiatives (interventions that focus on promoting data use culture by improving data availability and usability, facilitating use of data by health workers for decision making and planning (routine and long-term) and breaking down barriers to data use) , understand the determinants of implementation outcomes and determine the effects of data use initiatives on quality of care and selected health outcomes

## Materials and methods

### 1. Study settings

Intervention and comparison districts will be purposively selected from Dar es Salaam & Dodoma and Tanga & Mwanza Regions respectively with a view to minimizing contamination between intervention and comparison arms. In each region, the study area will include 20 health facilities, i.e., 10 health facilities from each district council. Health facility surveys will be conducted at baseline and end line in both the intervention and comparison areas, whereas the data use intervention will reach only the intervention district councils (two districts each in Dar es Salaam (Temeke and Kinondoni) and Dodoma (Dodoma City Council & Chamwino). The intervention districts will also be followed up at 6 months to measure the implementation outcomes and their determinants. To contextualize the settings of this study, we describe the study sites and the program.

#### a. Study sites

The intervention districts will be selected purposively based on the fact that the data use interventions will be implemented. The control districts will be selected from two regions to match the intervention districts based on geographical location (urban vs. rural). The health facilities from the selected districts were selected based on the following criteria: a primary public health facility, providing services for more than a year. Hereunder the characteristics of the selected districts are described.

Kinondoni and Temeke are urban districts (Municipality) in the Dar es Salaam Region, the business capital of Tanzania Mainland. The census of 2012 showed that the population of Kinondoni was 1,775,049 whereas that of Temeke District is 1,368,881.

Chamwino and Dodoma City councils are districts in Dodoma Region, the administrative capital of the united republic of Tanzania. The census of 2012 showed that the population of Chamwino was 330,543, whereas that of Dodoma city council was 410,956.

Tanga city council and Korogwe are districts in the Tanga region, one of the important cities in the coastal zone of the country. The census of 2012 showed that the population of Korogwe was 56,282 whereas that of Tanga city council was 273,332.

Mwanza city council and Misungwi District council are districts in Mwanza region, one of the important cities in the Lake zone region of the country. The census of 2012 showed that the population of Mwanza city council was 706,453 whereas that of Misungwi was 351,607.

The eight councils represents a mixture of metropolitan (Temeke & Kinondoni), urban (Dodoma City council, Mwanza city council, Tanga city council) and rural district councils (Chamwino, Korogwe and Misungwi). The study areas are suitable of generating outcomes that could easily be transferable to other similar settings in the country.

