#### 2) Understand the initial (baseline) situation of data use in the study settings in relation to decision making and comprehensive (council or health facility) planning

To understand the baseline situation, the four councils implementing the data use initiative will be matched equally with comparable councils where the data use interventions will not be implemented. Stratified sampling (to distinguish the level of facilities) will be used in these four councils to select a representative sample of facilities to be observed for one year after the project is implemented. This step combines quantitative and qualitative methodologies to evaluate the current state of data use in the recipient health facilities.

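### On the stated urban/rural matching factor the named councils are 3:1 (intervention) against 2:2 (control), and the two metropolitan intervention councils have no metropolitan control

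*Protocol article*

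**What the plan says.** Study sites, in the protocol article, gives one matching factor for councils, and it has two levels: "The control districts will be selected from two regions to match the intervention districts based on geographical location (urban vs. rural"). The baseline step under Study components adds that "the four councils implementing the data use initiative will be matched equally with comparable councils" outside the programme. The Abstract and the Study design section also describe the comparison as matched.

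The arms are named. Study settings lists the intervention councils as "two districts each in Dar es Salaam (Temeke and Kinondoni) and Dodoma (Dodoma City Council & Chamwino"). Study sites describes the remaining four, which are the controls: "Tanga city council and Korogwe are districts in the Tanga region" and "Mwanza city council and Misungwi District council are districts in Mwanza region".

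The closing paragraph of Study sites classifies all eight councils as a "mixture of metropolitan (Temeke & Kinondoni), urban (Dodoma City council, Mwanza city council, Tanga city council") and "rural district councils (Chamwino, Korogwe and Misungwi"). The same section also describes Kinondoni and Temeke as urban. Study settings allots 10 facilities to each council.

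**The concern.** The study is not randomised. Its counterfactual rests on control councils changing over the year as the intervention councils would have changed without the programme. Matching on setting is the protocol's stated support for that at council level. If the arms differ in their mix of settings, and settings have different underlying trends, part of the measured effect is a difference in setting. A reader told that the councils are matched on urban/rural location would assume that this source of confounding had been removed.

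**Working it through.** **Inputs.** Arm membership and 10 facilities per council come from Study settings and Study sites. The class of each council comes from the last paragraph of Study sites.

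**Check of the stated total.** 8 councils × 10 = 80 facilities, 4 × 10 = 40 per arm. This agrees with the 80 (40 + 40) given under Sampling and sample sizes.

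**Councils by arm.**

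| Class | Intervention | Control |
|---|---|---|
| Metropolitan | 2 (Temeke, Kinondoni) | 0 |
| Urban | 1 (Dodoma City) | 2 (Tanga City, Mwanza City) |
| Rural | 1 (Chamwino) | 2 (Korogwe, Misungwi) |

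**Two-level factor (the stated one, metropolitan counted as urban).**
- Intervention 3:1, or 30 and 10 facilities (75/25). Control 2:2, or 20 and 20 facilities (50/50).
- Possible 1:1 pairs: min(3, 2) + min(1, 2) = 3.
- One urban intervention council is left over (10 of 40 facilities, 25%), as is one rural control council.
- Intervention facilities with no control of the same stated class: 0 of 40.

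**Three-level classification.**
- Possible 1:1 pairs: min(2, 0) + min(1, 2) + min(1, 2) = 2.
- Intervention facilities with no metropolitan control: 2 × 10 = 20 of 40 (50%).

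**What the mix does to the contrast.** Let m, u and r be the mean changes that would occur without the programme in metropolitan, urban and rural facilities. Assume that each is the same in both arms and that facilities count equally.
- Intervention arm: 0.50m + 0.25u + 0.25r.
- Control arm: 0.50u + 0.50r.
- Difference with no true effect: 0.50m − 0.25u − 0.25r = 0.25(u − r) + 0.50(m − u).

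Stratifying by urban/rural and standardising to the intervention mix gives, in the urban stratum, (2m + u)/3 − u = (2/3)(m − u), and zero in the rural stratum. The weighted total is 0.75 × (2/3)(m − u) = 0.50(m − u). Stratification removes the 0.25(u − r) term and leaves the metropolitan term untouched. That is why the metropolitan councils need separate reporting.

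Dodoma City and Chamwino are 1:1 urban to rural, the same mix as the controls. That contrast is balanced on the stated factor as it stands.

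**Precision cost** (equal variances and independent units assumed; the ratios are the same with facilities or councils as the unit).
- Unstratified: 1/40 + 1/40 = 0.0500.
- Standardised: 0.75² × (1/30 + 1/20) + 0.25² × (1/10 + 1/20) = 0.0469 + 0.0094 = 0.0563. Ratio 1.125, so the standard error is √1.125 = 1.06 times as large.
- Dodoma City and Chamwino against all controls: 1/20 + 1/40 = 0.0750. Ratio 1.5, so the standard error is √1.5 = 1.22 times as large.

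**The case against.** **The limitation is already acknowledged.** The Discussion says that facilities across the four regions vary and that unidentified confounders may remain without randomisation. That is fair as a general caution. However, setting is an identified factor. The caution presents matching as applied and does not disclose that the one named matching factor is unbalanced.

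**Equal matching may mean only equal numbers, four councils with four.** That reading of the baseline step is possible. It does not rescue the Study sites statement, which names urban/rural location as the basis of the match.

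**Facilities are matched too, and sampling is stratified by facility level.** The Abstract and Discussion mention the first, and Study components the second. Both may make facilities more alike, but neither can change which councils are in each arm.

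**The intervention councils were set by the programme, and separate regions limit contamination.** Both are sound reasons for the design, and neither is disputed here.

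Some stronger readings are tempting but are not supported:
- A reader might infer that half the intervention facilities have no comparator. The stated factor has two levels, the protocol also calls Temeke and Kinondoni urban, and two urban control councils exist. Only the absence of a metropolitan control can be claimed for those 20 facilities.
- A reader might take the larger populations of the metropolitan councils as proof of bias. Population is not a matching variable, each council contributes 10 facilities, and nothing in the document links council population to facility trends.
- A reader might infer that the analysis ignores setting. Regression is planned without a list of covariates, and such a list may well stand in an analysis plan that is not shown.

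**Conclusion.** The point holds as a mismatch within the document. The named councils do not deliver the urban/rural match that the protocol claims. The shortfall on the stated factor is one of four intervention councils (10 of 40 facilities). On the three-level classification, 20 of 40 intervention facilities lack a metropolitan control.

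The counts rest only on the protocol's own labels and on 10 facilities per council. The Study design section speaks of twenty intervention facilities, which is a separate inconsistency. The 25% and 50% shares would be the same if those twenty were spread evenly over the four councils.

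The weights of 0.25 and 0.50 on trend differences follow from the council mix. The trend differences themselves are not given, so the size and direction of any bias cannot be stated. They would be zero if all settings shared one trend.

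**What to change.** 1. In Study sites and in the baseline step of Study components, replace the matching claims with the actual composition: 3:1 against 2:2 on urban/rural, with no metropolitan control. Bring the other references to matching into line, and name the imbalance among the limitations.
2. Estimate the intervention-control difference in change within urban and rural strata, standardised to the 75/25 intervention mix. Alternatively, include setting-by-time terms in the regression already planned.
3. Report Dodoma City and Chamwino against the control councils separately from Temeke and Kinondoni. State that the metropolitan result rests on urban controls that are not metropolitan.
4. State that region remains confounded with arm in every one of these contrasts. No analysis can remove this, because the two arms share no region.

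The councils and the data collection stay as they are. The cost is wording, modest analysis work and precision. On the assumptions in the working, the standard error rises by about 6% for the standardised estimate and about 22% for the contrast of Dodoma City and Chamwino with the controls. The latter also rests on only two intervention councils from one region, so it should be read as support for the main estimate and not as a replacement for it.

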#### b. Description of the data use initiatives

This implementation study is conducted in the context of an intervention that is set to promote data use for decision making and planning to improve the quality of care and health status (outcomes) of the population.

The President’s Office ‐ Regional Administration and Local Government (PO-RALG) requested assistance from UNICEF and USAID to promote and institutionalize a culture of data use at subnational level in the stride forwards to achieve universal health coverage (UHC) and strengthen PHC systems in line with the decentralization policy and related approaches such as the direct health facility financing (DHFF) . USAID engaged the Data for Implementation (Data.FI) project, to support the implementation of the request with the aim of using quality data to support evidence-based health programming and accountability.

In April 2021, UNICEF and Data.FI drafted a proposed joint implementation plan to support implementation of data use for this quality improvement initiative at different levels of the health care system, with Data.FI, providing support at national, regional and council level whereas UNICEF supports the health facility level. The intervention strategies aim to address 1) organizational determinants of data use (governance, equipment & tools and planning ) 2) technical determinants of data use (physical infrastructure, ICT infrastructure , HIS design and operability 3) behavioral determinants of data use (capability, opportunity and Motivation )

### 2. Study design

This study will adopt an effectiveness-implementation type-2 hybrid design [22] to evaluate the effectiveness of the data use initiatives in improving quality of health service delivery and health outcomes while simultaneously understanding the implementation of the initiatives. Since the data use initiative is implemented in twenty health facilities of two regions, we plan to carry out a before and after controlled design to estimate the combined effects of the data use initiatives in the intervention sites and matched control regions. Simultaneously we plan to assess the implementation processes of the initiatives and this entails the integration of both quantitative and qualitative data collection, analysis, and interpretation methods (i.e. mixed methods) to understand the implementation processes and the influencing factors.

